#### Moderators

*Demographic information* of the TAY, parents/caregivers and therapists will be gathered at T0, T4 and T5 by asking questions about gender, age, ethnicity, education level, work experience and income.

*Type and severity of problems* will also be measured with the SCID-5 Junior [71], YSR [72] and the CBCL [73] at T0, T4 and T5.

*Psychopathology of parents/caregivers* will be measured with the Adult Self-Report (ASR) [92] at T0, T4 and T5. The ASR contains 69 items that are rated on a 3-point Likert scale ranging from 0 = “*not true*” to 2 = “*very true or often true*”. The psychometric properties of the ASR are considered as good [92].

At T0, *treatment expectancy* will be measured with the Parent Expectancies for Therapy Scale (PETS) [93], which is revised for TAY. The PETS contains 7 items that are rated on a 6-point Likert scale ranging from 0 = “*fully disagree*” to 5 = “*fully agree*”. This questionnaire has also been used in previous research [94].

Information about *previous treatments* (including complementary and self-help treatments) will be gathered with the inventory of History of Treatments (VEHI) [95] at T0. The VEHI contains 8 questions in which participants indicate what previous treatment they received. This questionnaire has also been used in previous research [94].

#### Mediators

*Psychological flexibility* will also be included as a mediator for some of our outcomes (e.g., number of DSM-5 diagnoses). We have chosen to also include psychological flexibility as a mediator, as based on earlier studies, we expect that due to ACT your way, TAY will become more psychologically flexible, which in turn will lead to less psychological problems [52].

*Emotion regulation* will be measured with the Emotion Regulation Skills Questionnaire – Junior (ERSQ) [96] and the FEEL-KJ [97, 98] at T0, T2, T4 and T5. The ERSQ measures a broad set of emotion regulation strategies, including emotional awareness, integration of physical sensations and emotions, emotional clarity, understanding of emotions, influencing emotions, accepting emotions, tolerating emotions, willingness to endure difficult situations to achieve goals and self-support. The ERSQ contains 27 items that are rated on a 5-point Likert scale ranging from 0 = “*not at all*” to 4 = “*(almost) always*”. Research investigating the psychometric properties of the ERSQ is still ongoing, but preliminary results show that the internal consistency and construct validity are good ([name], personal communication, June 2021). At T1 and T3 a short version of the ERSQ will be used. The short version has been developed using factor and reliability analyses. From each subscale, the item with the highest factor loading and item-total correlation were selected (i.e., 9 items in total).

The FEEL-KJ measures a broad set of emotion regulation strategies that are used in response to anger, sadness and anxiety. The FEEL-KJ contains 90 questions (30 questions for each emotion) that are rated on a 5-point Likert scale ranging from 0 = “*almost never*” to 4 = “*almost always*”. In the current study, we will ask participants to answer the 30 questions solely for their most extreme emotion (i.e., either anger, sadness or anxiety). The FEEL-KJ has adequate psychometric properties [99].

*Self-compassion* will be measured with the Self-Compassion Scale Short Form (SCS-SF) [100–102] at T0, T2, T4 and T5. The questionnaire contains 12 items that are answered on a 7-point Likert scale ranging from 0 = “*seldom or never*” to 7 = “*almost always*”. The psychometric properties of the SCS-SF have been established in earlier research [100, 101].

The Autonomy Adolescent Questionnaire (AAQ) [103] will be used to measure *autonomy* at T0, T2, T4 and T5. The AAQ divides autonomy into three main categories: attitudinal, emotional and functional autonomy. The AAQ contains 18 items that are rated on a 5-point Likert scale ranging from 0 = “*not all true for me*” to 4 = “*totally true for me*”. The factor structure, convergent validity and divergent validity of the AAQ has been supported in earlier research [103].

*Perfectionism* will be measured with the Frost Multidimensional Perfectionism Scale (FMPS) [104] at T0, T2, T4 and T5. The FMPS consists of 35 questions that are rated on a 5-point Likert scale ranging from 0 = “*strongly disagree*” to 4 = “*strongly agree*”. The reliability and validity of the FMPS is established in earlier studies [104]. In the current study, we only use the subscales: personal standards, organization, concern over mistakes and doubt about actions, containing 26 questions in total. To reduce the burden for TAY, we excluded the subscales: parent expectations and parental criticism as we believe that how TAY view their parents’ expectations and criticism will not be targeted within the intervention.

*Self-esteem* will be measured with the Rosenberg Self-Esteem Scale (RSES) [105, 106] at T0, T2, T4 and T5. The RSES contains 10 questions that are rated on a 4-point Likert scale ranging from 0 = “*totally agree*” to 3 = “*totally disagree*”. Earlier research demonstrated the validity and test- retest reliability of the Dutch RSES [105].

For TAY who receive ACT your way or TAU in a group, *group cohesion* will be measured with the Group Climate Questionnaire-Short (GCQ-S) [107] at T1, T2, T3 and T4. The GCQ-S was revised for TAY. The questionnaire contains three subscales (i.e., Engagement, Conflict and Avoidance) and 12 items that are answered on a 7-point scale ranging from “*totally disagree*” to “*totally agree*”. The reliability and validity of the GCQ-S has been demonstrated as good [108, 109].

#### Other characteristics

*Treatment integrity* will be established by video/audio recording two randomly chosen ACT your way sessions per client (in the case of individual therapy) or group (in the case of group therapy). The sessions will be rated by an independent researcher with a checklist that has been developed in an earlier study [44]. The checklist is based on ACT literature and input from various ACT experts. The checklist can be used to assess which of the six core processes of ACT (i.e., acceptance, defusion, contact with the present moment, self as context, values and committed action) and ACT techniques (i.e., psychoeducation, mindfulness exercises, metaphors and experiential exercises) are carried out per session and if the goal of the session is obtained.

*The content of TAU* will be measured with a short version of the Therapy Procedure Checklist (TPC) [110] at T1, T2, T3 and T4. For each client, therapists fill out how many sessions took place after the previous assessment moment. Then, for each session, therapists indicate which techniques they used in the session (e.g., CBT or psychoeducation), if the session was individual or in a group and if the session was online or offline (for TAU only).

The Life Event Scale (LES) [111] will be used to gather information about several *life events* at T0, T4 and T5. The LES contains 23 questions about various life events (e.g., drug abuse, bereavement, maltreatment and suicide attempts). For each life event, participants are asked to indicate when the event took place (i.e., “*last week”, “last year”, “more than one year ago”*) and to what extent the event made them upset (i.e., ranging from 0 = “*not*” tot 3 = “*very*”). The LES has been used in previous research [94].

*Costs* will be measured with a cost diary based on the Trimbos Institute and Institute of Medical Technology Assessment Questionnaire on Costs Associated with Psychiatric Illness (TiC-P) [112] and PRODISQ [113]. With the cost diary, we will register direct healthcare costs (e.g., visits to healthcare professionals or alternative care), direct non-healthcare costs (e.g., formal and informal care), indirect costs (e.g., productivity losses caused by absence and reduced productivity and school) and out of pocket costs (e.g., transport or parking costs). The cost diary has been used in previous research (e.g., [114]).

### Data analysis

Both intent-to-treat and per-protocol analyses will be executed. Possible baseline differences in demographic characteristics, diagnostic characteristics and psychological flexibility between participants in the ACT your way and TAU condition will be checked by performing t-test (continuous variables) and chi-square analyses (categorical variables). Variables that differ between both conditions will be entered as covariates in all analyses.

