#### Sample size calculation

We calculated the sample size for a two-level multilevel analysis, using the Optimal Design program [64]. In accordance with our planned analyses, the first level represents the TAY and the second level represents the therapists. As most of the therapists either give the ACT your way or the TAU intervention, we calculated the sample size as for a cluster RCT in which the therapists represent the clusters. Within our sample size calculation, we used a cluster size (i.e., the expected number of therapists) of 70, as we expect that in both conditions approximately 35 therapists will be carrying out either the ACT your way or TAU intervention. In addition, we used an ICC of 0.05 as this is the average ICC reported in meta-analyses of therapist effects in psychological intervention research [65]. Furthermore, the effect size is based on a meta-analysis in which 39 RCT’s were included that investigated the efficacy of ACT, including 1,821 adults with various mental disorders [21]. We based the effect-size on this meta-analysis as, to our knowledge, this is the most recent meta-analysis examining the effects of ACT transdiagnostically. When ACT was compared to TAU a medium effect was found (Hedges g = 0.64), when ACT was compared to CBT a small effect was found (Hedges g = 0.32). In this study ACT will be compared to TAU, presuming a medium effect around 0.64. However, since we want to be conservative and expect that, at least with some of the participants, CBT will be used in TAU as well, an effect size of 0.50 was included in the sample size calculation. Hence, with a cluster size of 70, an effect size of 0.50, an ICC of 0.05, an α of 0.05 and a power of 0.8, a sample size of 140 (i.e., on average two TAY per therapist, and 70 TAY per condition) is assumed.

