### Study design and procedure

The study is designed as a multi-center, randomized controlled trial (RCT). Data will be collected in 14 Dutch and Belgian mental healthcare institutions. Within each institution, TAY meeting the inclusion/exclusion criteria, their parents/caregivers and their therapists will be asked to participate in the study. Parents/caregivers of adolescents younger than 16 will be directly involved in the study. TAY aged 16 and older will be asked first for permission to contact their parents/caregivers. If they agree, their parents/caregivers will be asked to participate in the study as well. Before enrolling in the study, written informed consent from TAY and parents/caregivers/legal representatives (for adolescents younger than 16) will be obtained. If parents/caregivers and therapists agree to participate, they will be asked for their own written informed consent as well.

In total, six multiple informant (TAY, parents/caregivers, therapist) assessments will be conducted: at baseline (T0), after 3 sessions (T1), after 6 sessions (T2), after 9 sessions (T3), at post-intervention (T4) and at 6-month follow-up (T5). Assessments will include diagnostic interviews (at T0, T4 and T5) and questionnaires (at T0 to T5). The assessments will be conducted by research assistants working at the participating institutions (e.g., master students and psychologists). Research assistants will be trained in administering the diagnostic interview and questionnaires. The TAY will receive a 30 euro gift card as a reward (5 euros per assessment). After the baseline assessment (T0), TAY will be randomly assigned to either the ACT your way or TAU condition using a computer generated block design. At each institution, five participants will be randomly allocated to the ACT your way condition and five participants will be randomly allocated to the TAU condition (blocksize = 10). See Fig. 1 for an overview of the study design.

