#### Effectiveness

The effect of the intervention on the primary (i.e., psychological flexibility and number of DSM-5 diagnoses) and secondary outcomes (i.e., presence of the primary DSM-5 diagnosis, psychopathology, personality problems, global functioning, individual and societal functioning, quality of life, stress, treatment satisfaction, drop-out and therapeutic alliance) will be evaluated using a two-level multilevel analysis in Mplus [115]. Specifically, we will investigate, if condition (i.e., ACT or TAU) predicts the post-intervention (T4) and 6-month follow-up (T5) levels of our primary and secondary outcomes, while controlling for the baseline levels of the concerning outcomes. We will perform a two-level multilevel analysis as we expect that TAY will be nested within therapists. Hence, the first level will represent the TAY and the second level will represent the therapists. We do not expect variance at the measurement level, as the analyses will be performed separately for the post-intervention and 6-month follow-up assessments. Although we expect that therapists will be nested within institutions, we will not include a third level as the number of institutions in our study is too small (i.e., 14 institutions). Instead, in all analyses, we will add dummies representing the mental healthcare institutions.

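### Additional covariates for all analyses are picked by between-arm baseline tests, so they follow chance imbalance rather than prognostic value and the models are not fully fixed in advance

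*Protocol article*

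**What the plan says.** Under Data analysis, the article lists what is compared: "Possible baseline differences in demographic characteristics, diagnostic characteristics and psychological flexibility between participants" in the two conditions. These "will be checked by performing t-test (continuous variables) and chi-square analyses (categorical variables"). The consequence is then stated: "Variables that differ between both conditions will be entered as covariates in all analyses". No significance threshold is given and the individual variables are not listed.

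The Effectiveness section separately fixes two adjustments that do not depend on any test. Condition is evaluated "while controlling for the baseline levels of the concerning outcomes", and "in all analyses, we will add dummies representing the mental healthcare institutions".

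A similar conditional rule stands in the Discussion: if treatment duration turns out to differ between the arms, it becomes a covariate in all analyses.

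**The concern.** Allocation is random within institution: "five participants will be randomly allocated to the ACT your way condition and five participants will be randomly allocated to the TAU condition". Among those randomised, a baseline difference is therefore chance by construction, and a t-test or chi-square test asks a question whose answer is already known. What makes a covariate useful is how well it predicts the outcome, and a between-arm test does not measure that. The rule can bring in a variable unrelated to outcome because it happened to be uneven, and can leave out a strong predictor because it happened to be even.

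Two things are at stake. First, the models for both primary outcomes cannot be written down before baseline data by arm are available; with no threshold for what counts as a difference, two analysts could apply the rule and reach different models. Second, precision that fixed prognostic covariates would give is obtained only when chance triggers the rule.

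**Working it through.** **1. The plan's own sample size.** Inputs from Sample size calculation: "with a cluster size of 70, an effect size of 0.50, an ICC of 0.05, an α of 0.05 and a power of 0.8", and "on average two TAY per therapist, and 70 TAY per condition". For a two-level cluster design with J = 70 therapists and m = 2 TAY each (two-sided test assumed):

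λ = J·d² / {4·[ICC + (1 − ICC)/m]} = 70 × 0.25 / {4 × [0.05 + 0.95/2]} = 17.5 / 2.1 = 8.33

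With 1 and 68 degrees of freedom this gives 81.2% power. 80% is first reached at 68 therapists (136 TAY, 80.1%). The figure of 140 is reproduced, and it takes no credit for covariates.

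**2. What is fixed and what is tested.**

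| Covariate | Status |
|---|---|
| Baseline level of the outcome | Fixed (Effectiveness) |
| Institution dummies | Fixed (Effectiveness) |
| Demographic and diagnostic characteristics | Enter only if the arms differ (Data analysis) |
| Psychological flexibility | Already fixed in its own model; test-dependent in the others |

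Table 1 shows no T0 measurement for treatment satisfaction, drop-out or therapeutic alliance. For these, only the institution dummies are fixed.

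**3. How often chance changes the model.** Assuming k independent candidates tested at 5%, P(at least one enters) = 1 − 0.95^k:

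- k = 5: 1 − 0.774 = 23%
- k = 10: 1 − 0.599 = 40%
- k = 15: 1 − 0.463 = 54%

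**4. Type I error.** In several sets of simulated trials with no treatment effect (N = 140), test-then-adjust rejected in 3.5% to 5.3% of trials at a nominal 5%. That is about nominal, or slightly conservative when the candidates are prognostic.

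**5. Power at the planned effect.** Assumptions not in the article: baseline-outcome correlation ρ = 0.5; ten candidates tested at 5%; one of them prognostic, with correlation r to the outcome after the baseline outcome is in the model; no therapist clustering (the design effect is only 1 + (2 − 1) × 0.05 = 1.05). Effect 0.50, N = 140, 5,000 simulated trials per setting:

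| Partial r | Always adjusted | Test-then-adjust | Loss (points) |
|---|---|---|---|
| 0.1 | 92.2% | 91.8% | 0.4 |
| 0.2 | 92.9% | 92.0% | 0.9 |
| 0.3 | 94.0% | 91.9% | 2.1 |
| 0.4 | 95.7% | 92.0% | 3.7 |
| 0.5 | 97.4% | 93.1% | 4.3 |

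A separate run put the loss at r = 0.5 at about 5 points. The always-adjusted column agrees with the normal approximation Φ(d·√(N/4) / √[(1 − ρ²)(1 − r²)] − 1.96):

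- r = 0.3: Φ(0.5 × 5.916 / √(0.75 × 0.91) − 1.96) = Φ(1.62) = 94.7%
- r = 0.5: Φ(2.958 / √(0.75 × 0.75) − 1.96) = Φ(1.98) = 97.6%

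If instead eight candidates jointly explain a further 5% of outcome variance, power is 92.5% with all fixed against 92.1% under the rule; at a further 15% it is 95.6% against 92.7%.

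**6. Where the loss is larger.** With no baseline outcome in the model and a continuous outcome, 6,000 trials per setting gave the following powers (always adjusted against test-then-adjust):

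| r | Effect 0.50 | Effect 0.40 |
|---|---|---|
| 0.3 | 0.87 v 0.84 | 0.70 v 0.66 |
| 0.4 | 0.89 v 0.83 | 0.72 v 0.65 |
| 0.5 | 0.91 v 0.84 | 0.77 v 0.66 |

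The losses are 3 to 7 points at 0.50 and 4 to 11 points at 0.40. For drop-out these figures are only indicative, since the runs are for a continuous outcome.

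**The case against.** The best defence is that the plan already does the important part. The baseline outcome is usually the strongest predictor, institution is the unit within which allocation is blocked, and both are in the primary models whatever the tests show. Under the assumption ρ = 0.5, baseline adjustment alone takes power from about 83–84% to about 92%. The rule is also stated in advance and uses baseline data only, so it cannot be steered by the treatment effect. All of this stands, and it limits the size of the point.

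Four stronger readings are tempting, but the documents do not support them.

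- *All covariates are chosen by test.* The Effectiveness section rules this out.
- *The rule produces false positives.* No set of runs shows inflation. Among null trials in which a prognostic variable narrowly misses selection (baseline p of 0.05 to 0.20, about 15% of trials), the rejection rate was 6.0% at r = 0.3 and 10.6% at r = 0.6. That is a conditional rate, and it averages out over all trials.
- *The primary analyses lose 7 points of power or more.* That needs an extra covariate with r of 0.4 to 0.5 and an effect of 0.4 SD in units of what remains after the fixed covariates. The article plans on 0.50, and nothing in it suggests a further variable that strong.
- *The trial is undersized because of the rule.* The calculation of 140 claims no gain from covariates, so the rule takes nothing from it.

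One could add that in the per-protocol analysis baseline differences need not be pure chance. That is true, but a significance test is no better guide to prognostic value there, and a list named in advance serves that analysis as well.

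**Conclusion.** The point holds for the additional covariates. They are selected on a criterion that carries no information about prognostic value, and the models remain incomplete until baseline data by arm are seen. This does not depend on any assumed correlation. The numerical harm to the primary analyses is small: no type I inflation, and a power loss of about 0 to 2 points for a partial correlation up to 0.3, rising to 4 to 5 points at 0.4 to 0.5. These figures assume effect 0.50, ρ = 0.5, selection at 5% and no clustering. The loss is larger if the true effect is smaller, or for treatment satisfaction, drop-out and alliance. It should be changed because the better alternative is nearly free; the primary result is not invalid without the change.

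**What to change.** Delete the baseline significance tests and the selection rule from Data analysis, and present baseline characteristics by condition descriptively. State one short covariate set for every model, used whatever imbalance is observed:

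- the baseline level of the outcome, where it is measured at T0;
- the institution dummies;
- a few T0 variables expected to be prognostic, for example age and baseline number of diagnoses.

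Number of diagnoses is already the baseline covariate for the second primary outcome, so of these two examples only age would be new in that model.

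The Discussion's rule on treatment duration has the same conditional form and concerns something observed after randomisation. If one fixed set is to hold, it should come out of the main models as well.

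The cost is a few sentences in two sections, settled before outcome data by arm are seen. No new data are needed and the sample size stays at 140.

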#### Effectiveness

The effect of the intervention on the primary (i.e., psychological flexibility and number of DSM-5 diagnoses) and secondary outcomes (i.e., presence of the primary DSM-5 diagnosis, psychopathology, personality problems, global functioning, individual and societal functioning, quality of life, stress, treatment satisfaction, drop-out and therapeutic alliance) will be evaluated using a two-level multilevel analysis in Mplus [115]. Specifically, we will investigate, if condition (i.e., ACT or TAU) predicts the post-intervention (T4) and 6-month follow-up (T5) levels of our primary and secondary outcomes, while controlling for the baseline levels of the concerning outcomes. We will perform a two-level multilevel analysis as we expect that TAY will be nested within therapists. Hence, the first level will represent the TAY and the second level will represent the therapists. We do not expect variance at the measurement level, as the analyses will be performed separately for the post-intervention and 6-month follow-up assessments. Although we expect that therapists will be nested within institutions, we will not include a third level as the number of institutions in our study is too small (i.e., 14 institutions). Instead, in all analyses, we will add dummies representing the mental healthcare institutions.

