There are several meta-analyses showing that ACT is equally effective compared to well established evidence-based treatments (e.g., cognitive behavioral therapy; CBT) and superior to inactive control conditions (e.g., placebo or waitlist) and treatment as usual (TAU) in adults with depression, anxiety, pain, substance use and other types of psychopathology [21–24]. Moreover, in the United States, ACT is registered as evidence-based treatment for adults with chronic pain and depression [25]. Until now, less is known about the effectiveness of ACT for adolescents and young adults [26, 27]. Few studies investigated the effectiveness of ACT in adolescents and/or young adults with different types of problems, such as anorexia nervosa [28, 29], obsessive–compulsive anxiety [30], pain [31, 32], depressive symptoms [33, 34], autism spectrum disorder [35], social and school adaptation [36], social anxiety [37], posttraumatic stress [38], learning disabilities and anxiety [39], academic procrastination [40], trichotillomania [41], aggression [42] and antisocial behaviour [43]. These studies show promising effects. In addition, the effectiveness of the ACT your way intervention has recently been examined in a pilot study with 23 TAY with recurrent or chronic depression, who previously received CBT [44]. At posttreatment, 76.2% of the TAY did not meet the criteria for a depressive disorder anymore. Moreover, participants reported significant improvements in depressive symptoms, quality of life, perceived competence, and comorbid internalizing problems. In addition, the treatment drop-out was remarkably less (20.6%) compared to treatment drop-out in a CBT trial for the same target group of 12 to 21 year olds (ranging from 41 to 57%) [45]. Hence, results in terms of the effectiveness of ACT your way specifically, also seem promising. However, many of the abovementioned studies lack an adequate sample size, do not use a control group or randomisation, or are case studies. Furthermore, no research has been done in TAY with a wide range of psychological disorders, including comorbid, chronic and/or recurrent diagnoses. In addition, the cost-effectiveness of ACT in TAY has never been studied before.

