The presented study design has some potential challenges that could turn into limitations if not handled properly. Hence, for each potential challenge, a solution to overcome this challenge will be discussed. First, in the current study, ACT your way will be carried out both in an individual as in a group format, making it more difficult to isolate intervention effects from treatment modality effects. We decided to carry out ACT your way both individually as in groups, as both treatment modalities have their own potential advantages. For instance, group interventions might provide more opportunities for normalization, positive peer modeling and social support, whereas within individual interventions, therapists can more easily adapt exercises and subjects to the specific wishes and needs of each client. To isolate intervention from treatment modality effects, we will perform additional analyses in which we explore possible differences between both treatment modalities (see Method section). Second, the TAU condition might be heterogeneous in content and duration, which makes it challenging to compare the effects of ACT your way with the effects of TAU. To address this challenge, we will ask all therapists in the TAU condition to write down the content and duration of each session. Subsequently, we will investigate if there are differences in duration between ACT your way and TAU. If there are differences, the duration of treatment will be added as covariate in all analyses. Third, recruiting a sample of 140 TAY in 24 months could be challenging. To reach this sample size, we will cooperate with fourteen mental health care institutions in the Netherlands and Belgium. Moreover, to promote participation, we will give TAY a 30 euro giftcard as a reward and only use online questionnaires that TAY, parents/caregivers and therapists can easily fill out at home. Last, non-response and/or drop-out can also be a potential challenge. To minimize non-response, we built a website, including a system that automatically sends research assistants weekly updates via mail, that helps research assistants to monitor the assessment progress. At the website and in the weekly updates, research assistants can easily see which questionnaires are filled out or not and which ones are planned. With the help of this website and automatic mailing system, researchers can directly react to non-response and increase the response rate of the study. To minimize measurement drop-out, we will motivate TAY to continue participating by sending them thank you emails and newsletters and handing out a 5 euro gift card after each assessment. Moreover, when participants drop out of treatment, we will still ask them to fill out the post-intervention and follow-up assessments. Furthermore, to avoid potential bias due to drop-out, all analyses will be carried out according to the intention to treat principle.

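### The Discussion relies on intention to treat to avoid drop-out bias, but that principle cannot replace a missing T4 or T5 outcome, and the effectiveness models leave out the interim scores that could help

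*Protocol article*

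**What the plan says.** **Model.** Data analysis, Effectiveness, specifies a two-level model (young people within therapists). Condition predicts the T4 level and the T5 level of each outcome, adjusted for its baseline level and for institution dummies. The visits are fitted one at a time: "We do not expect variance at the measurement level, as the analyses will be performed separately for the post-intervention and 6-month follow-up assessments". No T1 to T3 score enters, and T4 does not enter the T5 model. Under Moderation and mediation, T1 to T3 scores appear only as mediators.

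**Drop-out.** The Discussion concedes: "Last, non-response and/or drop-out can also be a potential challenge". It lists measures to limit non-response, says that those who stop treatment will still be asked for T4 and T5, and ends with the claim that "to avoid potential bias due to drop-out, all analyses will be carried out according to the intention to treat principle".

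**Data available (Table 1).** AFQ-Y, a primary outcome, is measured in full at T0, T2, T4 and T5, and with 8 items at T1 and T3. BFS and ORS are measured at all six assessments. PSS is measured in full at T0, T2, T4 and T5, and in short form at T1 and T3. The other primary outcome, the number of DSM-5 diagnoses, is measured only at T0, T4 and T5, as are YSR, CBCL and ISIQ.

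**The concern.** Intention to treat settles which participants belong to the comparison and under which arm they count. It says nothing about what to do when an outcome was not obtained. The Discussion therefore names a remedy that cannot do the job assigned to it, and the stated models do not do it instead.

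At stake is the T4 and T5 contrast on a primary outcome. If young people who respond poorly by mid-treatment are more likely to miss T4, and this happens more, or differently, in one arm, those who remain are no longer comparable given baseline alone. The interim scores that would show this are already collected but stay outside the effectiveness models.

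**Working it through.** **1. The plan's own figure.** Inputs from Sample size calculation: "an effect size of 0.50 was included in the sample size calculation"; "an ICC of 0.05, an α of 0.05 and a power of 0.8"; J = 70 therapists; n = 2 participants per therapist ("on average two TAY per therapist, and 70 TAY per condition"). A two-sided test is assumed. Non-centrality for a two-level cluster trial:

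λ = J·d² / {4·[ICC + (1 − ICC)/n]} = 70 × 0.25 / {4 × [0.05 + 0.95/2]} = 17.5 / 2.1 = 8.33.

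With 1 and 68 degrees of freedom, power is 0.812, so 140 reproduces (J = 68, or 136 participants, gives 0.801). The margin above 0.80 is thin, so attenuation of the effect matters.

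**2. What a missing T4 contributes.** The stated model is f(Y4 | condition, Y0, institution, therapist). For a participant without Y4, the likelihood contribution is ∫ f(y4 | condition, y0, …) dy4 = 1, which carries no information on the condition effect. Maximum likelihood in Mplus does not change this while the interim scores are outside the model. The estimate is then that of the participants observed at that visit, and its bias is approximately

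E[e | observed, ACT] − E[e | observed, TAU],

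where e is the T4 residual after baseline. This is zero if loss depends on baseline only. It need not be zero if loss depends on an interim score.

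**3. Size.** All of the following are assumptions, not document figures: correlations T0–T4 0.5, T0–T2 0.6 and T2–T4 0.7; SD 1; true T4 effect 0.50; T2 effect 0.25 to 0.50 (results barely change over this range); logistic loss at T4 with slope 1 on T2, higher (worse) scores being more likely to be lost; 1,000,000 simulated participants per arm.

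| Loss at T4 (ACT / TAU) | Loss depends on T2 in | Stated model | Using T2 |
|---|---|---|---|
| 20% / 40% | both arms | 0.43–0.44 | 0.50 |
| 20% / 40% | TAU only | 0.36–0.37 | 0.50 |
| 20% / 20% | TAU only | 0.43 | 0.50 |
| 20% / 20% | both arms, same mechanism | 0.50 | 0.50 |

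In a second set-up, with six correlated waves and loss depending on T3, the overall loss was varied from 10% to 40%. The bias was 0.01 to 0.03 SD when both arms share one loss mechanism (the rates then differ slightly because the effect shifts T3), and 0.05 to 0.16 SD when only one arm's loss depends on T3. It was nil when loss depends on baseline only.

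If loss is unrelated to T2, both approaches are unbiased and the stated model has 6% to 9% more variance.

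**4. Limit of the remedy.** The last column assumes that T2 is always observed. In the 0.36 scenario, if half of those lost at T4 also lack T2, the estimate recovers only to 0.45. If all lack it, there is no gain.

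**The case against.** The strongest reply is that the Effectiveness section only states the analysis model. A baseline-adjusted comparison at each fixed visit is a standard choice, and separate fits are compatible with multiple imputation or auxiliary variables, which an analysis plan not shown here may specify. That stands. A reader might infer that fitting T4 and T5 separately is what causes the bias, or that the lack of a missing-data section in a condensed article is itself the fault. Neither follows. What remains is a remedy that the article does name and that cannot work as claimed, whatever another document adds.

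A reader might also infer that the protocol predicts unequal loss of outcome data. It does not. The aims expect less treatment drop-out under ACT your way, and the figures in the introduction (20.6% in the 23-person pilot, 41% to 57% in a CBT trial) are treatment drop-out too. Requesting T4 and T5 from those who stop treatment, monitoring non-response weekly and giving a gift card after each assessment all reduce the risk. They do not recover those who still fail to respond.

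It is also right that the number of DSM-5 diagnoses has no interim scores of its own, so for that primary outcome no repeated score is being ignored. And T1 to T3 are tied to sessions 3, 6 and 9, so early leavers may lack them.

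**Conclusion.** The point holds in a limited form. The Discussion should not offer intention to treat as protection against drop-out bias, and the stated effectiveness models do not provide that protection: a participant missing at T4 or T5 drops out of that visit's estimate even when interim scores were recorded.

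Whether this biases the result depends on how assessments are lost, for which the article gives no figure. Under assumed loss of 20% to 40% that depends on interim response and differs between arms in rate or mechanism, a true 0.50 SD is estimated at about 0.36 to 0.44. With equal loss and the same mechanism there is no bias. The attenuation reflects the assumption that worse-off participants are lost; if better-off TAU participants were lost instead, the effect would be overstated. The simulations treat a continuous outcome with its own interim score, such as AFQ-Y, and their sizes should not be carried over to the diagnosis count.

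**What to change.** Keep a separate condition effect at T4 and at T5. Bring a small set of already collected scores into the effectiveness analysis, either by full-information likelihood with auxiliary variables or by multiple imputation:

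- **AFQ-Y:** the full T2 score, and T1 and T3 on the 8 common items.
- **BFS, ORS and PSS:** their own interim scores.
- **All outcomes measured at both visits:** T4 to inform the T5 analysis.
- **Number of DSM-5 diagnoses and other outcomes measured only at T0, T4 and T5:** T4 for T5, and interim scores of other measures as auxiliaries; for the diagnoses, a model suited to a count.

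In the Discussion, replace the intention-to-treat claim with this method, its missing-at-random assumption and a delta-shift sensitivity analysis. Intention to treat can remain as the definition of who is analysed.

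The cost is extra analysis work in the same software, with no new data or visits. There are a few more parameters to estimate with 140 participants, about two per therapist and 14 institutions, so the auxiliary set should stay small. With complete data the estimates are practically unchanged. The gain is limited for early leavers who also lack T1 to T3.
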